# Outcomes and Health Economics of Stroke using Rhythmic Auditory Stimulation (OrcHESTRAS): a protocol for a pragmatic, decentralized, longitudinal, multi-phase, withdrawal with randomized re-treatment trial of MR-001 in chronic stroke

**DOI:** 10.1186/s13063-025-09415-3

**Published:** 2026-01-08

**Keywords:** Stroke rehabilitation, Rhythmic auditory stimulation, Gait, Neuromodulation, Digital therapeutics, Home-based intervention, Mobility, Walking, Neurorehabilitation, Healthcare resource utilization

## Abstract

**Background:**

Persistent gait deficits limiting mobility, independence, and quality of life are common after stroke. These deficits also increase fall risk, hospitalizations, and mortality, driving substantial clinical and economic burden. Interventions that improve gait may reduce these risks and associated costs. Rhythmic auditory stimulation (RAS) is a validated technique that enhances gait parameters, including speed, cadence, and stride symmetry in stroke rehabilitation. MR-001 is an autonomous neurorehabilitation system that delivers personalized RAS for home-based walking rehabilitation. This study incorporates pragmatic and controlled design elements, consistent with real-world implementation settings, to evaluate engagement, clinical effectiveness, durability of response, and health economic impact of MR-001 in people living with gait impairment after stroke.

**Methods:**

This decentralized, longitudinal trial combines a pragmatic single-arm intervention phase with a randomized re-treatment phase. Approximately 225 participants with chronic stroke and gait deficit will be enrolled. In Step 1, all participants receive 12 weeks of MR-001 therapy (30 min, 3 times per week) followed by a 12-week washout. In Step 2, participants are randomized to either 12 additional weeks of MR-001 or a 24-week extended washout. The primary endpoint is user engagement, defined as the proportion achieving at least moderate engagement during Step 1. Secondary endpoints include walking endurance, durability of gains, quality of life, activities of daily living, social isolation, and cognitive function. Exploratory analyses include changes to general mobility, effects of re-treatment, subgroup analyses by baseline function and engagement, proportion and predictors of responders, and healthcare resource utilization assessed through claims data.

**Discussion:**

This pragmatic trial evaluates MR-001, a technology-enabled, autonomous neurorehabilitation system. The design expands on earlier work to assess engagement, durability, and re-treatment while linking clinical outcomes to claims data to generate preliminary evidence on the economic impact of home-based RAS. Findings will inform strategies to optimize adherence, support payer reimbursement, and guide the integration of MR-001 into long-term stroke care.

**Trial registration:**

ClinicalTrials.gov NCT06051539. Registered on 20 September 2023 https://clinicaltrials.gov/study/NCT06051539.

## Administrative information

Note: the numbers in curly brackets in this protocol refer to SPIRIT checklist item numbers. The order of the items has been modified to group similar items (see http://www.equator-network.org/reporting-guidelines/spirit-2013-statement-defining-standard-protocol-items-for-clinical-trials/).

## Introduction

### Background and rationale {6a}

Stroke is a leading cause of long-term disability worldwide [1], affecting over 7 million individuals in the USA alone [2]. Gait impairment is among the most prevalent and persistent consequences, impacting an estimated 54–80% of stroke survivors [3–5]. Such impairments compromise safety, limit independence, and reduce quality of life, particularly among older adults recovering from stroke [6–8]. While advances in acute stroke care have improved survival, they have also contributed to a higher long-term burden of disability. More individuals are now living with chronic post-stroke impairments. Direct medical costs are projected to exceed $50 billion annually and may more than double by 2035 [9, 10]. Walking difficulty is a primary concern for many survivors and their families [11]. These gait problems often co-occur with cognitive and emotional challenges that further restrict participation [10]. Scalable interventions that improve mobility and reduce healthcare utilization could help offset these rising costs while delivering value to patients, providers, and payers.

Access to high-quality gait rehabilitation remains limited, particularly for individuals in the chronic phase of recovery. Most interventions are resource-intensive, clinic-based, and poorly suited for long-term home use [12, 13]. As a result, many stroke survivors are left with few options for continued progress. Clinical guidelines increasingly call for scalable, personalized strategies to support mobility and reduce disability [14, 15]. Rhythmic auditory stimulation (RAS) is a well-validated intervention technique that engages auditory-motor entrainment (AME), a neurophysiological process in which the brain synchronizes movement to rhythmic auditory stimuli, such as in music [16, 17]. This synchronization can enhance gait neuromotor control by activating intact motor networks and potentially bypassing impaired pathways [18, 19].

RAS has been shown to improve walking speed, cadence, symmetry, and stride length post-stroke [20–23]. Walking and music-based interventions may also yield cognitive and emotional benefits, such as improvements in mood, memory, executive function, and quality of life [24–34]. However, most RAS studies have focused on short-term, supervised interventions [20]. Technology-enabled systems delivering RAS without the need for direct clinical supervision may offer a more scalable and sustainable model of care.

To address this gap, MedRhythms developed MR-001, an autonomous neurorehabilitation system that delivers individualized RAS in the home. A pilot study with an early prototype of MR-001 demonstrated that a fully automated, music-based RAS session reduced walking energy cost by ~9% and improved gait asymmetries by over 20% in individuals with chronic hemiparesis [35]. In a recent randomized controlled trial (RCT) [36] of 87 individuals with chronic post-stroke gait impairment (average >8 years post-stroke), participants who used MR-001 three times per week for 5 weeks improved walking speed by 22%, more than double the gain seen in controls (*p* = 0.013). Notably, 40% of MR-001 users exceeded the minimal clinically important difference (MCID) of 0.16 m/s [37]. They were also 3.7 times more likely to achieve both the MCID threshold and the community ambulation threshold of ≥0.8 m/s (*p* = 0.011). These findings demonstrate that stroke survivors many years after their initial event are still capable of achieving clinically meaningful gains with MR-001. Moreover, improvements continued to accrue over the 5-week intervention without evidence of plateau, supporting the potential for continued benefit with ongoing use.

The current longitudinal study builds on these previous findings, integrating both pragmatic and traditional controlled trial elements to evaluate the MR-001 intervention in a broader eligible population, over an extended intervention duration, and including follow-up and re-treatment phases in a real-world setting to assess the durability and replicability of benefit. Critically, it prioritizes engagement—measured as the proportion of participants achieving at least moderate engagement over the 12-week intervention period—as the primary endpoint, recognizing that consistent use is essential for durable, long-term impact. The study, therefore, aims to characterize real-world adherence and usage patterns of home-based RAS in daily life. In parallel, the study includes exploratory analyses to assess the potential economic impact of MR-001 by linking clinical outcomes with healthcare claims data. Indeed, stroke-related disability is a major cost driver, often leading to falls, hospitalizations, and long-term care. A prior budget impact model projected substantial cost savings with MR-001 [38], but empirical data are lacking. This trial will explore whether mobility improvements with MR-001 might correspond to reduced healthcare utilization over 12 months, offering early insights to support cost-effectiveness evaluations and the role of digital neurorehabilitation in value-based stroke care.

### Objectives {7}

This study aims to evaluate user patterns of engagement, clinical effectiveness, durability of response, and health economic impact on participants post-stroke who complete the MR-001 intervention in the home setting. The primary objective is to assess engagement with the MR-001 neurorehabilitation system, measured by the proportion of participants achieving at least moderate engagement over the 12-week intervention period. The secondary objectives are to evaluate: (1) the effects of MR-001 on walking endurance, as measured by the 6-Minute Walk Test (6MWT); (2) the durability of this effect following 12 weeks of intervention; and (3) the effects of MR-001 on health-related quality of life, activities of daily living, social isolation, and cognition and executive function. Exploratory objectives include assessing: (1) changes in general mobility, as measured by the Timed Up and Go Test (TUG); (2) the effects of a second period of treatment on walking endurance and general mobility following a 3-month no-intervention period; (3) the differential intervention effects across subgroups (e.g., engagement and baseline gait impairment subgroups); (4) the proportion and predictors of responders; and (5) healthcare resource utilization, assessed through claims data analysis.

### Trial design {8}

This longitudinal, pragmatic, decentralized hybrid trial integrates home-based implementation of the MR-001 therapy with selected controlled trial elements to maximize external validity while maintaining scientific rigor. In this study, “home-based” refers to any environment outside of a professional healthcare facility consistent with the FDA definition [39]. A two-step, withdrawal with randomized re-treatment (delayed randomization) design allows assessment of treatment engagement, clinical outcomes, durability of benefit, and the effects of re-treatment in the home setting. This hybrid design allows for evaluation of both immediate and sustained effects of the intervention, as well as the potential benefit of reintroduction following initial use. Spanning ~52 weeks, the study follows a decentralized design without traditional clinical trial sites. In-person assessments are conducted at more than 30 designated physical assessment center locations across the USA, chosen to ensure broad geographic representation of the population.

Step 1: All participants receive 12 weeks of MR-001 intervention (30 min per session, three times per week), followed by a 12-week washout. The 12-week intervention period was selected based on (1) extending the established evidence that users do not plateau after 5 weeks of MR-001 intervention [36] and (2) stroke rehabilitation evidence supporting this duration as effective for achieving clinically meaningful gains in walking capacity [40]. This timeframe also aligns with guidelines recommending sustained, task-specific therapy to support neuroplasticity and motor learning [14], and reflects typical US outpatient rehabilitation reimbursement models, which frequently authorizes approximately 36 therapy sessions over 12 weeks [41]. Participants self-administer MR-001 in their home environment, with remote support provided by the study team throughout the 12-week intervention period.

Step 2: At the end of the washout, participants are randomized 1:1 to either receive the MR-001 intervention for another 12 weeks followed by 12 weeks of washout, or continue with an additional 24-week washout. Participants and investigators are unblinded to the Step 2 allocation, but in-person assessors remain blinded.

Assessments occur at baseline and weeks 12, 16, 24, 36, and 48, with continuous falls/adverse event tracking and healthcare resource utilization (HRU) data collection over ~52 weeks. Collected outcomes include gait performance (6MWT), patient-reported outcomes (Barthel Index [BI; Step 1 only], PHQ-8, PROMIS Social Isolation), and cognitive tests (Trail Making Test A and B [TMT A and B; baseline and week 12 only]). Figure 1 illustrates the study design.

**Fig. 1 Fig1:**
[figure not shown]
Study design

## Methods: participants, interventions, and outcomes

### Study setting {9}

This decentralized, US-based clinical trial uses designated physical assessment centers—primarily through Velocity Clinical Research and Advanced Clinical Institute—for in-person gait performance assessments and clinical evaluations. Consistent with FDA guidance on decentralized trials [42], these locations serve exclusively as assessment venues and do not operate as investigational sites of record; personnel at these centers are not considered study staff, and they have no principal investigator, on-site study team, or regulatory responsibilities. At study initiation in October 2023, 30 such assessment centers were trained and launched. Assessment centers were strategically selected across US regions to ensure broad geographic representation. Assessment center selection began with 57 potential locations. Each location was evaluated using demographic and epidemiologic criteria, including population characteristics (city, state, county), age distribution, stroke prevalence and incidence (CDC data), covered lives by state (Flexpa database, including Medicare), and population diversity (race/ethnicity, languages spoken). Assessment centers with overlapping geographies were excluded. Figure 2 illustrates the locations of the selected assessment centers.

**Fig. 2 Fig2:**
[figure not shown]
Assessment center locations across the USA. Image generated using batchgeo.com

Intervention sessions are self-administered in the home setting, supported remotely by the Contract Research Organization (CRO), Curavit Clinical Research, via secure digital platforms and teleconsultations.

### Eligibility criteria {10}

#### Inclusion criteria (all must be met)

Equal to or greater than 6 months post-stroke with gait impairmentAge 18–85 years inclusiveUnderstand and speak EnglishAble to ambulate without assistance from another person (assistive devices allowed and must be used consistently)Willing to travel to a clinical testing location to complete in-person assessmentsAble to walk at a speed greater than or equal to 0.4 m/s* on 6-Minute Walk Test*Walking speed criterion selected to ensure adequate performance of MR-001

Must have claims data available and consent to sharing

#### Exclusion criteria (any of the following)

Hearing impairment such that the participant cannot hear the rhythmic stimulation of the musicPain that impairs walking abilityUnable to safely participate in walking sessions as determined by the investigatorRequires more than one rest during the 6-Minute Walk TestSignificant comorbid medical or neurological conditions that could impact gait or prevent safe participation (e.g., Parkinson’s disease, cerebral palsy, multiple sclerosis, myasthenia gravis, muscular dystrophy, spinal cord injury, recent major surgery within 3 months)Pregnant or become pregnant during the studyLower limb prostheticMore than 2 falls in the previous monthNon-reciprocal gait pattern (must have a 2-point step pattern)Treatment with a gait-based investigational intervention within the last 3 monthsUnable or unwilling to provide informed consent

### Who will take informed consent? {26a}

Informed consent is obtained remotely, and electronically, by qualified study personnel who have received appropriate training in Good Clinical Practice (GCP) and the specific requirements of this protocol. All individuals obtaining consent must be listed on the delegation log and have documented training in the informed consent process.

### Additional consent provisions for collection and use of participant data and biological specimens {26b}

No biological specimens are collected in this study. Participants provide specific consent for the collection and use of healthcare resource utilization data from insurance claims databases. Participants also consent to the use of de-identified data for future research purposes and potential sharing with regulatory authorities and scientific community through publications and presentations.

## Interventions

### Explanation for the choice of comparators {6b}

This study uses a withdrawal with randomized re-treatment design. The rationale for this design includes:

Established safety and efficacy: A prior RCT demonstrated that MR-001 leads to superior improvements in walking outcomes compared to unassisted walking without increasing adverse events [36]. These results provide strong evidence of efficacy and safety, making a full RCT unnecessary for Step 1 of this trial. Instead, all participants receive the intervention to establish patterns of real-world user engagement and adherence, which is the primary endpoint of interest in this pragmatic study.Ethical considerations: Given the potential benefits of RAS therapy and the limited access to such interventions for chronic stroke patients, it was deemed more ethical to provide all participants the opportunity to receive the intervention.Implementation evidence: The design allows for assessment of intervention durability and the impact of treatment interruption in an approximation of a real-world setting, providing valuable insights for implementation.

### Intervention description {11a}

MR-001 (MedRhythms, Inc., Portland, ME, USA) is an autonomous neurorehabilitation device that administers RAS. MR-001 is commercially available in the USA as a prescription medical device under the brand name, InTandem®, for physical rehabilitation of ambulatory adults with chronic stroke walking impairments. For a detailed overview of the MR-001/InTandem neurorehabilitation system, see Awad et al. [36]. In brief, the system continuously assesses the user’s entrainment to the target tempo and evaluates gait symmetry and variability, while safely and autonomously adjusting the target walking speed without direct clinician input. The system consists of:

Shoe-worn inertial sensors: Two shoe-worn wearable inertial sensors that measure walking patterns and gait parameters in real timeTouchscreen control unit: A kiosked (locked) touchscreen control unit preloaded with autonomous intervention software that processes gait data and delivers personalized therapyHeadset: Audio delivery systemCharging equipment: For maintaining device functionalityInstruction for Use (IFU) manual: Physical booklet containing detailed guidance on the proper operation, safety warnings and precautions, and clinical application of MR-001 to ensure safe and effective use

Participants use MR-001 for 30 min per session, three times per week, for a total of 12 weeks (approximately 36 sessions). The walking program is conducted independently in the home environment. The system provides a personalized intervention, with proprietary, adaptive algorithms that progress the therapy based on participant gait patterns and biomechanics.

While the MR-001 device is commercially available in the USA, it is distributed for investigational use in this study to evaluate additional clinical outcomes distinct from those in the commercial device’s current labeling. The device has been determined to be non-significant risk according to FDA criteria (21 CFR 812.3(m)), as it is not an implant, does not support or sustain life, and does not represent substantial risk to participant health or safety. The study, therefore, met abbreviated requirements for investigational device exemption (21 CFR 812.2(b)(1)).

### Criteria for discontinuing or modifying allocated interventions {11b}

Modification to the duration and/or frequency of the MR-001 intervention is not pre-specified in the protocol. Participants may discontinue the intervention based on the following criteria:

Participant request to withdraw from the interventionAdverse event that poses safety risks or significantly impacts participant well-beingInvestigator determination that continued participation poses safety risksA change in participant medical status that results in the participant meeting an exclusion criterion that contraindicates safe participation

Each walking session with MR-001 should be completed within the required 30-min timespan and should not be split throughout the day. Participants may elect to complete more than three sessions per week during the intervention phase, if discussed with study investigators and no safety concerns are raised.

### Strategies to improve adherence to interventions {11c}

Several strategies are employed to optimize participant adherence:

Onboarding support: Participants receive training on device use and study expectations via a guided setup call upon receipt of the device in their home. This simulates the education a patient might receive from a provider when obtaining a prescription.Flexible scheduling: Participants can choose their preferred times and locations for walking sessions within safety guidelines (e.g., not on a treadmill or busy streets) as noted in the protocol and described in the participant-facing Instruction for Use manual that is provided to all participants with the MR-001 system.Technical support: Access to a dedicated technical support hotline for device-related issues, which mirrors the optional support available from the manufacturer (MedRhythms, Inc.) for commercialized devices.Regular contact and reminder systems: Scheduled check-ins with study staff to address questions and provide support. Weekly engagement emails sent during the walking phase. Optional text/email reminders for appointments. Check-in calls when a participant has not walked for at least 7 days.

### Relevant concomitant care permitted or prohibited during the trial {11d}

#### Permitted concomitant care

Standard medical care and medications as prescribed by treating physiciansPhysical therapy and occupational therapy (must be documented)Use of assistive devices for mobility (must remain consistent throughout the study)Participation in general exercise programs not specifically targeting gait

#### Prohibited concomitant care

Participation in other investigational interventions targeting gait or mobilityInitiation of new intensive gait-specific rehabilitation programs during the study periodUse of other gait-based treatments or similar interventions

### Provisions for post-trial care {30}

No specific post-trial care is provided by the sponsor, but participants are encouraged to discuss ongoing rehabilitation needs with their healthcare providers. If participants request information about the commercial availability of MR-001, they are sent an email with an attached InTandem Information Kit and links to the InTandem website [43] and an informational video.

### Outcomes {12}

The primary endpoint is participant engagement with the MR-001 neurorehabilitation system, operationalized as the proportion of participants achieving at least moderate engagement over the 12-week treatment phase. Engagement will be categorized as low, moderate, or high based on predefined thresholds of weeks, sessions, and minutes of use, with the proportion of participants achieving at least moderate engagement defined by exceeding a benchmark of 60%. Session completion will be recorded automatically by the device’s usage logs, with higher counts indicating greater adherence to the prescribed rehabilitation regimen.

Secondary endpoints include:Walking endurance: Change in distance walked on the 6MWT [44] from baseline to the end of the 12-week intervention. The 6MWT measures the maximum distance an individual can walk on a flat surface in 6 min, with greater distances reflecting improved endurance and mobility.Durability of response: Change in 6MWT distance from the end of the intervention to the end of the subsequent washout period, to assess whether mobility gains are maintained without ongoing treatment.Depressive symptoms: Change in scores on the Patient Health Questionnaire-8 (PHQ-8) [45], an 8-item self-report measure of depressive symptom severity (score range: 0–24; higher scores indicate more severe symptoms).Activities of daily living: Change in the BI [46] score, which rates independence in basic daily activities such as feeding, bathing, dressing, and mobility (score range: 0–100; higher scores indicate greater independence).Social isolation: Change in scores on the PROMIS Social Isolation Scale [47, 48], which assesses perceived isolation from others, with higher T-scores indicating greater isolation.Cognitive function: Change in completion time for TMT Parts A and B [49, 50], neuropsychological measures of processing speed (Part A) and executive function/set-shifting (Part B), where shorter completion times indicate better performance.

Exploratory endpoints include:6MWT results collected during the re-treatment phase (Step 2 of the study).TUG [51] test results in both Step 1 and Step 2, assessing functional mobility by timing the participant rising from a chair, walking 3 meters, turning, returning, and sitting (shorter times indicate better mobility).Subgroup analyses: Assessing differential intervention effects on primary, secondary, and exploratory outcomes across engagement levels and baseline gait impairment.Clinical responsiveness: Assessing the proportion of responders (i.e., participants who achieve at least the minimal clinically important difference (MCID) on the 6MWT) to help quantify the proportion of patients experiencing a clinically meaningful benefit.Predictors of response: To assess which subgroups may benefit most from the intervention, baseline demographic and clinical characteristics, as well as engagement levels with the device, will be examined as potential predictors of responder versus non-responder status.Healthcare resource utilization assessed through claims data analysis, including total all-cause healthcare encounters (outpatient visits, emergency department visits, and hospitalizations) and the proportion of participants with all-cause emergency department visits and hospitalizations from baseline through ~52 weeks.

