## Statistical methods

### Statistical methods for primary and secondary outcomes {20a}

Primary analysis: The primary endpoint is engagement with MR-001, defined as the proportion of participants achieving at least moderate engagement. Engagement will be categorized as low, moderate, or high based on predefined thresholds of weeks, sessions, and minutes of use. The primary hypothesis is that the proportion of participants achieving at least moderate engagement exceeds a benchmark of 60%. Sensitivity analyses will be conducted at thresholds of 70% and 80%. A one-sided binomial proportion test will be used at significance level *α* = 0.05. Participants who initiate the intervention but withdraw from the study prior to completion of the planned intervention will be classified as non-engaged in the primary analysis.

Secondary analyses: Secondary endpoint analyses will evaluate mean changes from baseline to post-intervention for walking endurance (6MWT), depressive symptoms (PHQ-8), independence in activities of daily living (BI), social isolation (PROMIS Social Isolation Scale), and cognitive and executive function (TMT A and B).

Durability of walking endurance will be assessed at 16-week and 24-week follow-up visits after discontinuation of the intervention at 12 weeks. Results at these follow-up visits will be compared with the post-intervention assessment to determine whether the gains achieved during treatment are sustained. The analysis will be conducted using a non-inferiority framework, with a pre-specified margin of one-half of the minimal clinically important difference (17.2 m) [52]. This approach is designed to test whether the benefits observed during the intervention period are retained after device use is discontinued. Linear mixed modeling (LMM) will be used to estimate the changes over time. Random intercepts and/or modeling the covariance matrix of the error terms will be used to account for repeated measures. Model choices will be made based on minimizing Akaike Information Criteria (AIC) and Bayesian Information Criteria (BIC). Age, sex, baseline speed, and time since stroke will be evaluated and included as covariates if they are predictive of the change scores.

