### Methods for additional analyses (e.g., subgroup analyses) {20b}

#### Exploratory analyses

Exploratory analyses are planned to provide additional insight into the effects of MR-001 and to identify factors that may influence treatment response. These will include:

Change in general mobility (TUG): Mobility will be assessed at multiple study visits across the intervention, follow-up, and re-treatment phases. Analyses will explore whether the MR-001 intervention is associated with sustained or progressive improvements in functional mobility, as well as whether gains are maintained after withdrawal or re-established with re-treatment.Clinical responsiveness: Participants who achieve at least the minimal clinically important difference (MCID) on the 6MWT will be classified as responders. This analysis will help quantify the proportion of patients experiencing a clinically meaningful benefit, complementing the mean change analysis.Predictors of response: Baseline demographic and clinical characteristics, as well as engagement levels with the device, will be examined as potential predictors of responder versus non-responder status. This analysis is intended to inform which subgroups may benefit most from the intervention.Durability of re-treatment: Among participants who undergo a second round of intervention following the withdrawal phase, changes in walking mobility and endurance will be compared before and after re-treatment to assess whether the intervention effect can be re-established.

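### Comparing the primary endpoint across engagement levels is circular, and Step 1 subgroup and predictor contrasts show associations with change, not differential benefit

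*Protocol article*

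**What the plan says.** Outcomes {12} lists, as an exploratory endpoint, subgroup analyses "Assessing differential intervention effects on primary, secondary, and exploratory outcomes across engagement levels and baseline gait impairment". Objectives {7} repeats the aim and names engagement and baseline gait impairment as example subgroups.

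The primary endpoint is built from the same variable. Section {20a} states: "The primary endpoint is engagement with MR-001, defined as the proportion of participants achieving at least moderate engagement". Outcomes {12} adds: "Engagement will be categorized as low, moderate, or high based on predefined thresholds of weeks, sessions, and minutes of use".

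The exploratory analyses in section {20b} use engagement again, as a predictor of 6MWT response: "Baseline demographic and clinical characteristics, as well as engagement levels with the device, will be examined as potential predictors of responder versus non-responder status". The stated purpose follows: "This analysis is intended to inform which subgroups may benefit most from the intervention".

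Step 1 has no comparator. Section {6b} regards the earlier trial's results as "making a full RCT unnecessary for Step 1 of this trial". Step 2 has one: "At the end of the washout, participants are randomized 1:1 to either receive the MR-001 intervention for another 12 weeks", with the others continuing washout and in-person assessors blinded ({17a}). The re-treatment item in {20b}, however, is worded as a before-after comparison among the re-treated: "changes in walking mobility and endurance will be compared before and after re-treatment".

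**The concern.** Three separate problems sit under one heading, and each has its own reach.

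- **Circularity.** Engagement level cannot be a subgroup for an outcome that is engagement level. This affects only that pairing.
- **Selection on engagement.** Engagement is observed after treatment starts. Participants may choose extra sessions after discussion with investigators ({11b}), and those who start and then withdraw are counted as non-engaged ({20a}). People who are fitter or already improving may use the device more, and people doing badly may fall into the lowest stratum. This affects the engagement strata and engagement as a predictor. Engagement is also unknown when the device is prescribed, so it cannot identify in advance whom to treat.
- **No Step 1 control.** A subgroup difference in change is not a difference in treatment effect. This affects every Step 1 subgroup and every responder predictor. For a baseline-gait subgroup there is a further possible artefact: the screening 6MWT supplies both the eligibility check and the starting value for the change ({10}, {13}, Table 1), so its measurement error would enter both the subgroup and the outcome.

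At stake is what may be concluded about who benefits. As worded, a gradient by engagement or by baseline gait could be reported as a differential effect even if MR-001 did nothing.

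**Working it through.** **The plan's own figures.** No figure is given for the subgroup or predictor analyses. The only power figure is for the primary test: 98% for 72% against 60%, one-sided 0.05 ({14}). The exact binomial test with 225 participants rejects at 148 or more successes (attained alpha 0.0435) and has power 98.3%, so the figure reproduces. It does not bear on this point, except that 72% of 225 serves as an example below.

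**Step 1: the circular pairing.** At least moderate engagement is 0% in the low stratum, 100% in the moderate and 100% in the high. At the assumed 72%, 0.72 x 225 = 162 and 225 - 162 = 63, so the comparison is 0/63 against 162/162. Nothing is estimated.

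**Step 2: engagement strata with no treatment effect.** Assumptions, none in the protocol: SD of 6MWT change 40 m; correlation r = 0.1 to 0.3 between engagement and the change that would have happened anyway; 72% engaged. Under normality the difference, engaged minus not engaged, is r x SD x phi(z)/(0.72 x 0.28), with z = -0.583 and phi(z) = 0.337, so the last factor is 1.67.

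- r = 0.1: 0.1 x 40 x 1.67 = 6.7 m (simulation 6.8 m)
- r = 0.3: 0.3 x 40 x 1.67 = 20.0 m (simulation 20.1 m)

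**Step 3: baseline-gait halves with no treatment effect.** Assumptions: the subgroup is a median split on the screening 6MWT; SD 100-120 m; test-retest ICC 0.90-0.98. The protocol gives neither SD nor ICC. The spurious extra gain in the slower half is 2 x 0.798 x SD x (1 - ICC).

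| SD | ICC | Formula | Simulation |
|---|---|---|---|
| 100 m | 0.90 | 16.0 m | 16.0 m |
| 100 m | 0.98 | 3.2 m | 3.2 m |
| 120 m | 0.90 | 19.2 m | 19.1 m |
| 120 m | 0.98 | 3.8 m | 3.6 m |

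Section {20a} gives 17.2 m as the margin of half the minimal clinically important difference (MCID); reading 17.2 m as the half, the MCID is 34.4 m. The artefact is then 3.2/34.4 = 0.09 to 19.1/34.4 = 0.56 of an MCID. Apparent responders, slower against faster half, are 4.9% against 3.6% at the mildest setting and 32% against 21% at the strongest. A second simulation applied the entry threshold (0.4 m/s x 360 s = 144 m), with an assumed mean of 300 m, SD 80-120 m and ICC 0.90-0.97. It gave 3.7 to 16.5 m.

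**Step 4: precision of the Step 2 alternative.** Take about 180 completers ({14}), equal halves, and an assumed change SD of 40 m in both periods.

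- Step 1 contrast, 90 against 90: 40 x sqrt(2/90) = 6.0 m
- Cohort-by-subgroup interaction, four cells of 45: 40 x sqrt(4/45) = 11.9 m, a 95% half-width of 1.96 x 11.9 = 23 m

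The ratio of standard errors is 2 whatever the SD.

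**The case against.** The strongest reply is that these are exploratory items in a condensed article. No alpha or power attaches to them, the language is cautious, and model details belong in the analysis plan. A 0%/100% table would mislead nobody. Most of this stands as a limit on weight: no primary or secondary inference is touched. It does not rescue the wording. An exploratory label does not make a tautology informative or turn an association into an effect, and the limitations in the Discussion mention neither the missing Step 1 control nor the post-baseline nature of engagement.

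Several stronger readings are tempting and not supported:

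- **That the whole subgroup plan is circular.** Engagement rate by baseline gait is a sound description, and other outcomes by engagement level are not tautological.
- **That all these analyses rest on uncontrolled data.** The exploratory outcomes include Step 2 6MWT and Timed Up and Go (TUG), and {20c} keeps Step 2 participants in their assigned groups. A cohort-by-subgroup model is not excluded. The before-after wording belongs to a separate item.
- **That regression to the mean drives the baseline-gait findings.** The article does not define baseline gait impairment; using the screening 6MWT is an inference. SD and reliability are assumed, the mildest case is trivial, and the calculation covers 6MWT change only.
- **That the plan sets out to decide who should receive the device.** It speaks only of informing which subgroups may benefit most.

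It may also be said that {20a} already considers baseline speed as a covariate. That is conditional on its predicting change. Adjusting for the variable that defines a baseline-gait subgroup largely removes the contrast; it does not correct it.

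**Conclusion.** The point holds in a limited form. One planned comparison, the primary endpoint by engagement level, is empty by construction; this needs no assumption. Step 1 contrasts by engagement level, by baseline gait and by responder predictor cannot carry the terms differential intervention effect or benefit, because Step 1 is uncontrolled. The engagement contrasts are in addition open to self-selection: 6.8 to 20.1 m with no treatment effect, under the assumed correlations and SD. A baseline-gait contrast taken from the screening 6MWT is open to regression to the mean of unknown size, about 3 to 19 m under the assumed SD and ICC. The documents cannot say whether either artefact will be large in this trial. The correction is worth making because it changes what can be claimed about who benefits.

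**What to change.** 1. In Outcomes {12}, remove the comparison of the primary endpoint across engagement levels. Keep engagement rate by baseline gait, labelled descriptive.
2. In {7}, {12} and {20b}, report Step 1 subgroup and predictor results as associations with change, and drop the wording about benefit for them. Adjustment for baseline 6MWT suits predictors other than baseline gait. It is not a remedy for the baseline-gait subgroup contrast.
3. Reserve the term differential effect for an exploratory cohort (A against B) by subgroup interaction on week 24 to 36 change in 6MWT and TUG. Fix the subgroups from screening gait and Step 1 engagement, both known before randomisation. Specify it before Step 2 outcomes are seen by cohort; otherwise label it post hoc.

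**Cost.** Wording and one model; the week 24 and week 36 tests are already in Table 1. The downside should be stated with the result. The interaction estimates the effect of re-treatment, not of a first course, and only in those who complete Step 1 ({16c}), so low engagers who withdrew are absent. Its standard error is about twice that of the Step 1 contrast with about 180 completers. With a half-width near 23 m under the assumed SD of 40 m, it may well be inconclusive.
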